## Results

### Study Outcomes

The primary outcome of this study is the percentage of patients with normalized BP (defined as SBP <140 mmHg and DBP <90 mmHg), as measured at the 12-month outpatient clinic visit. Secondary outcomes of this study are detailed in Textbox 3.

Secondary outcome measures.The percentage of patients with controlled BP (defined as SBP <140 mmHg and DBP <90 mmHg), as measured at the 3-month outpatient clinic visit.Patient satisfaction, as assessed by the patient satisfaction questionnaire [18].Health care utilization, defined as an outpatient clinic visit, emergency care visit, or admission for any reason. This factor will be measured via questionnaires and verified by EMR data.Major Adverse Cardiac Events (MACEs)a. Death of any causeb. Cardiac deathc. Recurrent STEMId. Recurrent NST-ACSe. Revascularizationf. Hospitalization for heart failureg. Transient Ischemic Attackh. Ischemic strokePropensity of medication adherence, measured by the 8-item Morisky Medication Adherence Scale (MMAS-8) [21].Physical activity, as measured by the iPAQ [20].Quality of life, measured by the SF-36 [19].Percentage of patients in which a previously unknown sustained arrhythmia (>30 seconds) is detected.Cost-effectiveness, expressed as the incremental cost-effectiveness ratio.

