## Methods

### Study Design (Design, Randomization, and Follow-Up)

*The Box* is a single-center open RCT, and is a parallel group study. The study will be conducted at the Leiden University Medical Center (LUMC), a tertiary care hospital in Leiden, The Netherlands. The trial is registered under clinical trial number NCT02976376 (Clinicaltrials.gov) and NL56453.058.16 (Toetsingonline.nl). After inclusion, patients will be randomized 1:1 to either *The Box* (intervention group) or to regular follow-up (control group). Block randomization per 10 participants will be performed. Randomization will be stratified per primary diagnosis (STEMI or NST-ACS) and per age (<50, 51-60, 61-70, 71-80, and >80 years). A website will be used to generate randomization lists [16].

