### Regular Follow-Up

Since 2004, the department of Cardiology of the LUMC has a dedicated care track for patients with STEMI or NST-ACS. Details about this protocol have been described previously by Liem et al [3]. Briefly, patients with signs and symptoms that are possibly related to a myocardial infarction are referred to a PCI center. Upon arrival, patients are immediately transferred to the catheterization department, where primary PCI of the culprit lesion is performed. Before discharge, patients are given written and oral information on the importance of medication adherence and lifestyle advices, in accordance with the European Guidelines on cardiovascular disease prevention in clinical practice [17].

After approximately 48-hours, patients are discharged from the hospital. The standard follow-up during the first year after discharge includes four outpatient clinic visits:

*Approximately 1 month after STEMI or NST-ACS*. This visit includes: a BP measurement; a 10-second, 12-lead ECG; laboratory testing (including kidney function, renal function, and lipid spectrum); and an interview with a doctor or nurse practitioner.*Approximately 3 months after STEMI or NST-ACS*. This visit includes: a BP measurement; a 10-second, 12-lead ECG; stress echo; a 24-hour Holter ECG, and an interview with a doctor or nurse practitioner.*Approximately 6 months after STEMI or NST-ACS*. This visit includes: a BP measurement, a 10-second, 12-lead ECG; a 24-hour Holter ECG; laboratory testing (including kidney function, renal function, and lipid spectrum); a transthoracic echocardiogram (TTE); and an interview with a doctor or nurse practitioner.*Approximately 12 months after STEMI or NST-ACS*. This visit includes: a BP measurement, a 10-second, 12-lead ECG; laboratory testing (including kidney function, renal function, and lipid spectrum); a TTE; and an interview with a doctor or nurse practitioner.

Patients who are randomized to regular follow-up receive the same care as patients who do not participate in the study. A flowchart of regular follow-up is detailed in Figure 1.

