### The Box

When randomized to *The Box* (Figure 2), patients will receive a box containing a weight scale, BP monitor, activity tracker, and a wearable ECG device. Patients will receive *The Box* before discharge and will be given the same written and oral information on the importance of medication adherence and lifestyle advices as the control group, in accordance with the European Guidelines on cardiovascular disease prevention in clinical practice [17]. The necessary apps will be downloaded on the patient’s smartphone; necessary accounts will be created and the installation of the devices will be carried out by a health care professional dedicated to the project. Afterwards, patients will be given oral instructions on the usage of the devices: they will be instructed to measure BP in a sitting position after five minutes of resting. The device should be applied to the left upper arm. Patients will be instructed to rest their left forearm on a table. Furthermore, a manual explaining the usage of the wearables (described below) will be handed over with *The Box*. Instruction videos are also available on YouTube. Patients who do not own a smartphone or tablet with iOS or Android OS but are willing to participate and be randomized to *The Box* will receive a smartphone. Patients will be instructed to use their own wireless Internet access (eg, home WiFi network). No mobile data network plan will be provided with the smartphone.

Patients will be instructed to record a single lead ECG, measure BP, and record their weight daily, preferably at the same time of day. Furthermore, participants will be asked to record a single lead ECG if any symptoms of possible cardiac origin occur (as interpreted by the patient). Lastly, patients will be instructed to wear their activity tracker during the day to track their daily number of steps, and at night to track the duration and quality of sleep. Patients will be told that measurements will be checked on a daily basis and that they will be contacted in cases of predefined data irregularities. Patients will be explicitly told that they cannot rely on the devices of *The Box* in emergency situations.

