In addition to daily measurements, the first and third of the four standard outpatient clinic visits will be replaced by an electronic visit, in which the patient will communicate with the doctor or nurse practitioner via a secured video connection. The content of the interview will be comparable to the content of a regular outpatient clinic visit. The same doctors and nurse practitioners will perform the regular outpatient clinic visits and the digital outpatient clinic visits. In the intervention group, the 10-second 12-lead ECG and the laboratory testing one month after the index event will not be performed. Moreover, the 10-second 12-lead ECG, the 24-hour Holter ECG, laboratory testing, and the TTE 6 months after the index event will not be performed (Figure 1).

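### The 140/90 primary outcome comes from a routine clinic visit in an open trial, and no common BP procedure or repeat-reading rule is described for both arms

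*Protocol article*

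**What the plan says.** Under Study Outcomes, the primary outcome is the proportion of patients whose SBP is below 140 mmHg and whose DBP is below 90 mmHg, "as measured at the 12-month outpatient clinic visit". The same definition at the 3-month clinic visit is the first secondary outcome.

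Under Regular Follow-Up, the contents of the 12-month visit are listed as "a BP measurement, a 10-second, 12-lead ECG; laboratory testing (including kidney function, renal function, and lipid spectrum); a TTE". A doctor or nurse practitioner also interviews the patient. On the control arm the section adds: "Patients who are randomized to regular follow-up receive the same care as patients who do not participate in the study".

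Under Study Design, the trial "is a single-center open RCT, and is a parallel group study". The Box section says: "The same doctors and nurse practitioners will perform the regular outpatient clinic visits and the digital outpatient clinic visits".

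For home readings, The Box section does describe technique: "they will be instructed to measure BP in a sitting position after five minutes of resting", with the cuff on the left upper arm and the forearm supported. Home values go into the department's medical record (Data Integration in Electronic Medical Records), where warnings fire at SBP above 139 and DBP above 89. Under Reasons to Adjust Therapeutic Regimen, the data reviewer discusses the data with the treating physician or nurse practitioner.

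**The concern.** A threshold outcome is sensitive to what happens after a high first reading: whether it is repeated, and which value is recorded. In an open trial that choice can depend on the arm.

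Here the information available is also unequal. For a Box patient, the clinician may have months of home values with which to discount a high clinic reading, and the alert system uses the same cut-points as the endpoint. No such data are collected for controls. More repetition in The Box is therefore plausible without bad faith.

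The planned Chi-square test takes the recorded classification as given, so it can neither detect nor correct a difference in how the classification was reached. The 3-month outcome has the same exposure.

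A separate and milder matter is random error. If the endpoint rests on one reading, patients near the threshold are often misclassified in both arms, which dilutes a true effect.

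**Working it through.** The plan has no figure of its own to reproduce here, since the article gives no BP SD or repeatability.

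**Inputs from the protocol article.** Threshold 140 mmHg systolic; control rate 75%; 200 patients randomised 1:1, so 100 per arm; Chi-square test.

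**Assumptions.** Between-patient SD (sb) 12-15 mmHg; within-patient SD (sw) 6-10 mmHg, independent between readings; normal distribution; SBP only; 75% controlled on the first reading in both arms; no true effect; two-sided 5% test, so 2.5% in favour of The Box by chance; the lower of two readings kept.

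**Step 1: patients who change class on a repeat.** The correlation of two readings is r = sb²/(sb² + sw²). The share with a high first and a controlled second reading is q = 0.75 - P(both below 140), from the bivariate normal distribution.

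- sb 15, sw 6: r = 225/261 = 0.862; P(both below) = 0.683; q = 0.067.
- sb 12, sw 10: r = 144/244 = 0.590; P(both below) = 0.633; q = 0.117.

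So q runs from 6.7 to 11.7 points. As a share of the 25% with a high first reading, that is 0.067/0.25 = 27% to 0.117/0.25 = 47%.

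**Step 2: spurious difference.** If a fraction fB of high readings is repeated in The Box and fC in controls, the difference is (fB - fC) × q.

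**Step 3: chance of a false result favouring The Box.** With d = p1 - p2 and p̄ the mean of p1 and p2, this is Φ((d - 1.96·s0)/s1), where s0 = √(2p̄(1-p̄)/100) and s1 = √((p1(1-p1) + p2(1-p2))/100).

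- d = 0.067 (81.7% v 75%): s0 = 0.0583, s1 = 0.0581; Φ(-0.81) = 21%.
- d = 0.117 (86.7% v 75%): s0 = 0.0557, s1 = 0.0550; Φ(0.14) = 56%.

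| High readings repeated, Box v control | Spurious difference (points) | False result favouring The Box |
|---|---|---|
| Equal in both arms | 0 | 2.5% |
| 75% v 50% | 1.7-2.9 | about 5-8% |
| 50% v 0% | about 3-6 | about 8-17% |
| 100% v 0% | 6.7-11.7 | about 21-56% |

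Against the planned difference of 95% - 75% = 20 points, 2-3 points is 10-15% and 7-12 points is 35-60%.

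**Step 4: sensitivity.** With total SD 16-20 and within-visit SD 4-10 mmHg, complete one-sided repetition gives 3.6-11.3 points if the lower value is kept and 1.9-6.9 if the two readings are averaged. A quarter of high Box readings repeated, none in controls, lower kept, gives 0.9-2.8. At a base rate of 85%, complete one-sided repetition with the lower kept gives 2.7-8.2.

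**Step 5: random misclassification.** The probability that the endpoint value and the patient's own mean fall on opposite sides of 140 is about 10-17% for one reading and about 6-10% for the mean of three (within-patient variance sw²/3).

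**The case against.** The strongest objection is that much of this could be read from silence. Naming a BP measurement among the visit's contents does not fix the number of readings or rule out a clinic procedure. The article refers to an earlier publication for the care track, and an article commonly leaves such detail to the full protocol. The BP measurement is listed apart from the interview, so the treating clinician need not be the one who takes it. Home technique is described because lay patients must be taught it, which does not show that clinic staff lack a procedure. Having the same staff for both arms also limits systematic differences in technique, and using a clinic reading in both arms is better than using home values that only one arm has.

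Most of this stands. A reader might infer that the endpoint is one unstandardised reading taken by unblinded treating staff. The documents do not say so. A reader might also take 7-12 points as the expected bias. That figure needs every high Box reading repeated, no high control reading repeated and the lower value always kept. Nothing in the documents suggests that pattern, and the same clinicians could equally repeat high control readings.

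The objection does not remove the exposure. The article itself ties a threshold outcome to a routine-care visit in an open trial, gives controls the same care as non-participants, and lets clinicians see home BP in one arm only.

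**Conclusion.** The concern holds as a risk of arm-dependent ascertainment that the described design leaves open. It is not shown that bias will occur. Its size depends on the pattern of repetition: about 2-3 points for a modest imbalance, about 3-6 if half of high Box readings and no control readings are repeated, and about 7-12 only in the extreme case. Even the modest case raises the chance of a false result favouring The Box from 2.5% to about 5-8%.

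All these figures rest on assumed SDs and on SBP alone; requiring DBP below 90 as well would change them. They also treat readings as independent around the patient's mean. If part of the within-patient variation is shared by readings at one visit, both the repeat-reading bias and the gain from averaging are smaller. The misclassification figures describe dilution in both arms, which is a matter of precision and not of validity.

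**What to change.** Define the BP endpoint at 3 and 12 months identically in both arms: a fixed number of automated readings (for example three), seated, after five minutes of rest, with the same device type, taken before the interview. Store every reading, define controlled BP on their mean, and state that readings repeated because of a high or low value do not count towards the endpoint. Clinicians remain free to take further readings for care.

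Both arms already attend in person at 3 and 12 months, so no visit and no extra assessor is needed. The cost is a few minutes per visit and one paragraph of protocol text. The downside is that the control rate under this procedure may differ slightly from the assumed 75%. If the full protocol already fixes such a procedure, one sentence stating it settles the point.

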**Methods:**

In this single center, open, randomized controlled trial patients who suffered from STEMI or NST-ACS will be randomized 1:1 to an intervention group or control group. Both groups will be followed up to one year after the index event. The intervention group will take daily measurements with a smartphone-compatible electrocardiogram device, blood pressure (BP) monitor, weight scale, and activity tracker. Furthermore, two of four outpatient clinic visits will be replaced by electronic visits (1 and 6 months after index event). The control group will receive regular care, consisting of four outpatient clinic visits (1, 3, 6, and 12 months after index event). All patients will be asked to fill in validated questionnaires about patient satisfaction, quality of life, propensity of medication adherence, and physical activity.

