### Economic Analysis

To assess the cost-effectiveness of the intervention, costs per quality adjusted life year (QALY) will be calculated. The analysis will be performed from a societal perspective with a time horizon of one year. Patients will receive a health care resource use questionnaire at 6 months and 12 months. In this questionnaire, a patient will be asked to fill in their total health care utilization, such as outpatient clinic visits, emergency visits, admissions for any reason, and visits to the general practitioner. All outpatient clinic visits, emergency visits, and admissions for any reason reported in the questionnaire will be verified by EMR data. In the same questionnaire, the patient will be asked to fill in total medication use. All health care and medication use will be multiplied with standard cost prices to calculate costs [22]. To calculate indirect costs, patients will be asked to note absence from paid and unpaid work. Productivity costs will be calculated using the friction cost method. Absence will again be multiplied against standard cost prices [22]. QALYs will be calculated from utility scores from the SF-36 questionnaire, which will be administered at baseline, 1 month, 6 months, and 12 months [19,23]. Finally, costs and QALYs in both groups will be compared. It is our hypothesis that societal costs will be lower in the intervention group.

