### Statistical Analyses

A power calculation was done using R software [24], which is based on a comparison of two proportions of patients with controlled BP (defined as an SBP of 139 mmHg or less and a DBP of 89 mmHg or less). We hypothesize that in the *The Box* group, 95% of the patients will achieve controlled BP, while in the control group, 75% will achieve controlled BP [25]. For this calculation, an alpha of 0.05, a beta of 0.20, and a margin of 0.07 were chosen, yielding a sample size of 200 patients.

Data will be analyzed according to the intention-to-treat principle. Causes of missing data will be tabulated (Multimedia Appendix 1). The percentage of missing data is expected to be low. Therefore, complete case analyses will be done. Analyses will be based on the missing-at-random assumption. If the percentage of missing values exceeds 7%, multiple imputation will be applied in the analysis of the data.

After finishing the study (defined as the last patient’s last visit), the proportion of patients with controlled BP will be compared with a Chi-square test. Logistic regression might be done if serious imbalances of baseline variables exist, to correct for potential confounding variables. Percentages of patients with controlled BP at three months (secondary outcome 1), and percentages of patients in which a previously unknown sustained arrhythmia is detected, will also be compared with a Chi-square test.

Scores of questionnaires (patient satisfaction questionnaire, MMAS-8 scale, iPAQ questionnaire, and SF-36 questionnaire) and health care utilization will be compared using an independent t-test. Major Adverse Cardiac Events (MACEs) will only be reported. As the study is underpowered, no statistics will be done on MACEs. The numbers will be hypothesis-generating.

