### Health Care Utilization

A concern regarding smart technology interventions is the fear that patients, given their nonmedical background and their perceived inability to interpreted medical data correctly, increase the number of contact points with hospitals, leading to more outpatient clinic visits and emergency department visits. This issue could therefore lead to higher burdens on both patients and health care staff, without improving clinical outcomes. Scientific evidence describing the relationship between increased monitoring frequency and health care utilization is scarce. Patients participating in this study will receive clear instructions about the usage of the devices, as well as the reasons for the hospital to contact the patients. It is therefore expected that health care utilization will not be higher in the intervention group.

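### Health care utilization pools scheduled with unscheduled clinic visits while The Box swaps two of four for electronic visits, so the comparison depends on an unstated counting rule

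*Protocol article*

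**What the plan says.** All references are to the protocol article.

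- **Outcome.** Study Outcomes (Textbox 3) gives "Health care utilization, defined as an outpatient clinic visit, emergency care visit, or admission for any reason", measured by questionnaire and verified against the electronic medical record. It draws no line between scheduled and unscheduled contacts.
- **Test.** Statistical Analyses says that questionnaire scores "and health care utilization will be compared using an independent t-test". It neither excludes scheduled visits nor adjusts for them.
- **Control schedule.** Regular Follow-Up: "The standard follow-up during the first year after discharge includes four outpatient clinic visits", at 1, 3, 6 and 12 months.
- **Box schedule.** The Abstract (Methods) says that "two of four outpatient clinic visits will be replaced by electronic visits (1 and 6 months after index event"), and the section The Box says that "the first and third of the four standard outpatient clinic visits will be replaced by an electronic visit".
- **Status of the electronic visit.** Those two sections set the electronic visit against the outpatient clinic visit. The resource questionnaire in Economic Analysis asks for "total health care utilization, such as outpatient clinic visits, emergency visits, admissions for any reason, and visits to the general practitioner" and does not name electronic visits. But The Box also says "The same doctors and nurse practitioners will perform the regular outpatient clinic visits and the digital outpatient clinic visits", and Patient Compliance uses the same digital/physical pairing.
- **Purpose.** The Discussion (Health Care Utilization) gives the worry as patients who "increase the number of contact points with hospitals, leading to more outpatient clinic visits and emergency department visits", and expects utilization in the intervention group not to be higher.

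**The concern.** The Discussion asks whether home monitoring prompts extra care seeking. The outcome as defined mixes that quantity with the number of clinic visits the schedule assigns, and the schedule differs between arms by design.

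If electronic visits are left out of the count, The Box starts about two visits per patient lower, before any patient seeks or avoids care. The stated expectation of no higher utilization is then met unless The Box adds more than two contacts per patient on average. If electronic visits are counted, the arms start level. The conclusion can therefore turn on a coding choice that the article does not state, in a trial where allocation is known.

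Some monitoring-driven activity is not named in the definition under either reading: the email or telephone contacts (Reasons to Contact Patients) and the 24-hour Holter recordings prompted by a home ECG (Single Lead Electrocardiogram).

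**Working it through.** The article gives no expected difference, SD or power for health care utilization, so there is no figure of its own to reproduce.

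**Inputs from the article.** Scheduled clinic visits: control 4; The Box 2 physical plus 2 electronic. Randomization 1:1 with 200 patients, so about 100 per arm. Two-sided alpha 0.05 is used for the test.

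**Assumed inputs.** SD of the yearly contact count: 2, 3 or 4. Complete follow-up in all 200.

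**Step 1: built-in difference (The Box minus control).**
- Electronic visits not counted: 2 - 4 = -2 visits per patient, half of the scheduled visits.
- Electronic visits counted: 4 - 4 = 0.
- Nonadherence lets Box patients ask for regular visits, and the analysis is by intention to treat. If a proportion p did so before the 1-month visit, the first figure becomes -2 x (1 - p), somewhat smaller than 2.

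**Step 2: offsetting.** If The Box adds x unscheduled contacts per patient, the pooled difference on the 4 v 2 reading is x - 2. It is -1 at x = 1, 0 at x = 2, and positive only beyond x = 2.

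**Step 3: how often a significant reduction is declared on the 4 v 2 reading.** With d the size of the net reduction,

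probability = Phi( d / (SD x sqrt(2/100)) - 1.96 ).

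| Assumed SD | Standard error | x = 0 (d = 2) | x = 1 (d = 1) |
|---|---|---|---|
| 2 | 0.283 | 7.07 - 1.96, giving 1.00 | 3.54 - 1.96, giving 0.942 |
| 3 | 0.424 | 4.71 - 1.96, giving 0.997 | 2.36 - 1.96, giving 0.654 |
| 4 | 0.566 | 3.54 - 1.96, giving 0.942 | 1.77 - 1.96, giving 0.424 |

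With unscheduled care unchanged, a significant reduction appears in 94-100% of trials. With one extra unscheduled contact per Box patient, it still appears in 42-94%.

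**Step 4: a second variance model.** Treat scheduled visits as constant and let unscheduled contacts have mean m and variance k x m in each arm (assumed m = 0.5 to 1.5, k = 1 to 3). With equal unscheduled care, z = -2 / sqrt(2 x k x m / 100):
- m = 0.5, k = 1: -2 / 0.1 = -20.
- m = 1.5, k = 3: -2 / 0.3 = -6.7.

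A significant reduction is practically certain across that range.

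**Step 5: unscheduled contacts only.** Take m = 1.0, k = 2, and suppose The Box doubles unscheduled care. The variance of the difference is 2 x (1 + 2) / 100 = 0.06, so the standard error is 0.245. The pooled 4 v 2 count gives -1.0 (z about -4.1); unscheduled contacts alone give +1.0 (z about +4.1). The same care yields opposite conclusions.

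**The case against.** **The stronger reading.** A reader might infer that the protocol removes two visits, so the comparison must show a reduction and must hide extra care. The documents do not support that. The visits are replaced by electronic visits with comparable interview content. The wording in The Box and Patient Compliance can be read as making the electronic visit a kind of outpatient clinic visit, and on that reading the gap is zero. Emergency visits and admissions are untouched by the schedule, and Economic Analysis collects them as separate items, so a rise in either can still be seen. Offsetting affects the pooled total, and the article does not say that only a pooled total will be reported.

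**Total utilization is a legitimate question.** Replacing visits is part of the intervention, and the Introduction cites patient burden and staff workload. Whether the replaced visits are outweighed by extra ones is a real net-effect question, and the article does not plan to claim a reduction. This stands. But the schedule-driven part is known before randomization. It belongs in the cost analysis and does not answer the worry set out in the Discussion.

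**Coding detail may sit in the full plan.** This is fair for the rule on electronic visits. However, the article does state a definition and a test, and it is their combination with the visit schedule that causes the difficulty.

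**The probabilities rest on assumed spreads.** True. The gap of two visits does not, apart from the counting rule and returns to regular visits.

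**The t-test.** Nothing here shows that a t-test on mean counts is wrong with about 100 per arm. A count model would be a preference and would not repair the definition.

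**Conclusion.** The point holds in conditional form. If electronic visits are not counted, which is the plainer reading of the Abstract, The Box and Economic Analysis, the comparison carries about -2 visits per patient from the schedule, less any returns to regular visits. A reduction would then largely restate the schedule, and up to about two extra unscheduled visits per patient could be offset in the pooled total. If they are counted, the built-in difference is zero. Under either rule the pooled count does not isolate the extra care seeking that the Discussion is concerned with.

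The 94-100% figure assumes an SD of 2 to 4, 100 patients per arm, the 4 v 2 reading and the full gap of two. This is a secondary outcome, so the change is advisable rather than critical.

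**What to change.** 1. State in the outcome definition whether an electronic visit counts as an outpatient clinic visit.
2. As the measure that answers the Discussion's question, compare unscheduled contacts between arms: outpatient visits beyond the four protocol time points, emergency visits and admissions. Regular visits at those four time points by Box patients who return to regular follow-up count as scheduled.
3. Report by arm, descriptively, the scheduled physical visits, the electronic visits and, where recorded, alert-driven email or telephone contacts and Holter recordings.
4. Leave the saving from replaced visits to the cost analysis.

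The cost is a wording change plus some coding to classify visits as scheduled or unscheduled, by a rule fixed beforehand because the trial is open. Outpatient visits, emergency visits and admissions are already collected and verified against the medical record. The article commits to monitoring reminders and no-shows but does not say that alert-driven contacts are logged, hence the qualifier in step 3. A count model is optional and not part of this correction.
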